**6.2.1. Power estimates for Specific Aim 2**

Sample size is selected to ensure sufficient accuracy for characterizing the operating characteristics (sensitivity and specificity) of 3-month finasteride PSA velocity and to have adequate power to detect the difference in PSA decline between cases and controls (non-cases). We estimate a positive biopsy rate of 40% in study subjects. Thus, the ratio of cancer cases to non-cases (controls) is 0.67(=0.4/0.6). With finasteride, a decline of 34% was seen in controls by 3 months[6]; a decline of 10-15% in cancer cases is assumed, corresponding to an additive change on a logarithmic PSA scale (in order to assume normality) of -log(1-0.34)=0.416 for controls, and -log(1-0.10)=0.105 to –log(1-0.15)=0.163 for cases. An estimate of the standard deviation of log PSA from the 3379 SABOR cohort is .89. Assuming a correlation of .5 between two PSA measures from the same patient (before and after finasteride) implies the same standard deviation for the difference or change in log PSA over 3-months. With these assumptions, a sample of 360 (144 cancer cases and 216 controls) in finasteride arm achieves a 75% to 90% power to test the null hypothesis that there is no difference between cases and controls in 3-month finasteride PSA change with a significance level (alpha) of 0.05 using a two-sided two-sample t-test (Table IX).

Table IX: Power for 216 Controls (no PCa) and 144 Cases (PCa) in Finasteride Arm

| PSA decline in | PSA decline in cancer cases | | | | |
| --- | --- | --- | --- | --- | --- |
| Controls | 8 % | 10% | 12% | 14% | 16% |
| 30 % | **.814** | **.747** | .665 | .574 | .479 |
| 32 % | **.884** | **.833** | **.766** | .687 | .598 |
| 34 % | **.934** | **.900** | **.851** | **.788** | .713 |
| 36 % | **.966** | **.944** | **.912** | **.867** | **.809** |
| 38 % | **.984** | **.973** | **.954** | **.926** | **.886** |
| 40 % | **.994** | **.988** | **.979** | **.963** | **.939** |

To minimize bias and eliminate the effects of unknown confounding variables on the effect of 3-month finasteride treatment in PSA change, a blinded placebo arm is included. The Medical Therapy of Prostatic Symptoms Research Group study[16], found that, among 670 men in placebo group, at year 1, the serum PSA level remained the same on average (the median change from baseline to year 1 was equal to 0). We thus anticipate that PSA will be unchanged in placebo arm for a 3-month period (i.e., average change is 0 in logPSA). With finasteride, weanticipate that the average decline in PSA is between 24.4% (=34%X0.6+10%X0.4) and 26.4% (=34%X0.6+15%X0.4), corresponding to an additive change of 0.28 (=-log[1-0.244]) to 0.31 (=1-log[1-0.264]) on a logPSA scale. We thus assume the average change is 0.3 in logPSA for finasteride arm. A sample of 450 (360 in finasteride arm and 90 in placebo arm) achieves an 81% power to detect a 0.3 difference in average logPSA change between finasteride and placebo with a type I error of 0.05 and an estimated standard deviation of 0.89 using a two-sided two-sample t-test. A 4:1 ratio of randomization scheme is a trade-off between a feasible sample size and adequate statistical power to detect a 0.3 difference in logPSA between finasteride and placebo (Table X).

**Table X:** Sample Size and Corresponding Power

| Sample size (finasteride) | Sample size (placebo) | Allocation ratio | Power |
| --- | --- | --- | --- |
| 360 | 36 | 0.1 (10:1) | 0.48 |
| 360 | 54 | 0.15 (6.67:1) | 0.63 |
| 360 | 72 | 0.2 (5:1) | 0.74 |
| **360** | **90** | **0.25 (4:1)** | **0.81** |
| 360 | 108 | 0.3 (3.33:1) | 0.86 |
| 360 | 126 | 0.35 (2.86:1) | 0.90 |

Our clinical experience suggests a 10% dropout for this three-month trial. The sample size is inflated to 500(=400/0.9). In SABOR, 1033 out of 3379 (30.6%) participants have an intermediate risk of prostate cancer.[44] Therefore, in order to achieve a sample of 400 eligible intermediate risk participants, we will need to screen 1308(=400/30.6%) men. We will accrue not only from SABOR subjects but from general Urology patients in whom over 1500 biopsies are performed annually.

Our sample size calculation is based on the expected sensitivity (or specificity) and the desired precision of the confidence interval (CI) for the sensitivity (or specificity). Our primary interest is whether a 3-month finasteride PSA velocity has a low false positive rate (high specificity) to reduce unnecessary biopsy for a fixed sensitivity. It is thus appropriate to estimate sensitivities less precisely than specificities. Our analysis[12] (1225 cancer cases vs. 4362 controls) found sensitivities ranging from 20 to 40% for specificities ranging from 80 to 95%. With 144 cancer cases, using the binomial formula, the standard error for sensitivities can be controlled within 4.1%. Similarly, with 216 controls, the standard error for specificities can be controlled within 2.7%.

**6.2.2. Analysis for Specific Aim 2**

Three-month finasteride/placebo PSA velocity will be determined for each participant by linear regression of the logarithmically transformed PSA using all four PSA values at baseline, 1, 2, and 3 months. The slope of the fitted regression line is the empirical estimate of 3-month finasteride/placebo PSA velocity for each individual. Differences between cases and controls will be accessed via a two-sample t-test on these slopes at the alpha=.05 level of statistical significance for finasteride and placebo arms separately. Sensitivities and specificities for 3-month finasteride/placebo PSA velocity will be calculated according to a range of cutoffs of velocity. For this application, lower values of velocity, generally negative in sign, (more steep declines) correspond to controls and higher values, generally positive in sign, (less declines) correspond to cases. The area underneath the receiver operating characteristic curve and corresponding 95%CI will be calculated. A test of null hypothesis of no predictive information (AUC=0.5) will be performed using Wilcoxon rank test and U statistics at the alpha=.05 level of statistical significance.[44]

Table III showed that PSA has better performance characteristics for the detection of high-grade disease than for overall risk of prostate cancer. Therefore, in our study, we plan to explore the operating characteristics of 3-month finasteride PSA velocity specifically for higher-grade (Gleason ≥ 7) cancers. The same test statistics (AUC, sensitivity and specificity) will be calculated as described before.

*Potential pitfalls and alternative strategies for Specific Aim 2*

The distribution of 3-month finasteride PSA velocity in cases and controls may not appear to be normally distribution by inspection of histograms, violating the Normal assumption required for the two-sample t-test. In this case the less powerful but robust nonparametric Mann-Whitney test will be used to compare the distributions. The definition of 3-month finasteride PSA on the log scale and corresponding cutoff are cumbersome to interpret because the log transformation is a nonlinear transformation. Therefore simpler more interpretable definitions of velocity will be evaluated and compared. One definition we have recently suggested is the percent change in PSA from baseline. This definition is less precise as it uses the first and last PSA measure as opposed to all PSA measures at each month as used by our proposed definition. Missing PSA observations will be a potential concern although we expect a low incidence. For individuals with only the first and last PSA available, 3-month finasteride PSA velocity can be alternatively defined as the difference in logPSA values divided by the difference in time points. The 3-month PSA endpoint will not be available from individuals who dropped out resulting in inability to make comparisons to the primary endpoint of PSA velocity and a reduction of sample size. In anticipation of incompleters, our targeted sample size of 360 subjects is inflated by 10%, for a total of 400 enrollees.

**6.3.** **Specific Aim 3**: To characterize the operating characteristics of serum PSA and DRE before and after 3 months of finasteride and compare to the 3-month finasteride ‘challenge’ as markers for disease.

*Rationale: We have advocated that newly proposed biomarkers should not be examined in isolation but rather calibrated against standard approaches, especially when the standard is cheaper and/or easier to measure. A single PSA is easier to use than computation of PSA velocity. Because of the cohort-dependent effect on PSA operating characteristic studies, we further emphasize that the comparison be made on the same cohort.*

**6.3.1. Power for Specific Aim 3**

The operating characteristics of 3-month finasteride PSA velocity will be compared to four additional markers: initial (before finasteride) PSA, 3-month finasteride PSA (current PSA value after 3 months on finasteride), initial DRE, and 3-month finasteride DRE (DRE result after 3 months on finasteride) on the same series of patients. The same power calculation as for Specific Aim 2 applies: sensitivities and specificities of these markers in the ranges 20 to 40% and 80 to 95%, respectively, can also be estimated with the same degree of accuracy (standard error within 4.1% for sensitivity; 2.7% for specificity) from 144 cases and 216 controls.

Based on the unbalanced sample size, tests of the null hypotheses that sensitivities and specificities of 3-month finasteride PSA velocity equals that of these alternative markers will obtain sufficient (80%) power to detect small elevations in specificities but relatively large elevations in sensitivities. This disadvantage is alleviated because we are primarily interested in the effect of 3-month finasteride PSA on increasing specificity. Specifically, with 144 cancer cases, the study will have 80 percent power to detect an increase of 13.5, 15.8 and 17.8 percentage points in sensitivity of 3-month finasteride PSA velocity relative to the sensitivities of 20%, 30% and 40% of the alternative markers, respectively. Conversely, with 216 controls, the study will obtain 80% power to detect increases of 8.6, 7.4, 6.1 and 4.3 percentage points in specificity of 3-month finasteride PSA velocity relative to the specificities of the other markers when the specificities equal 80%, 85%, 90% and 95%, respectively. The power calculations are based on the two-sided McNemar’s test with significance level of 0.05 using the midpoint method proposed by Lachenbruch(1992).[66]

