**6.5.4. Analysis for key objectives**

- Objectives 1 to 3

Tests of differences in the AUC between all pairs of markers (Objective 1: PCPT RC vs. PCA3 and PCPT RC vs. TMPRSS2:ERG; Objective 2: PSA velocity vs. PCA3, PSA velocity vs. TMPRSS2:ERG; Objective 3: posterior risk vs. PCA3, posterior risk vs. TMPRSS2:ERG) will be performed using the U-statistic approach of DeLong et al.[67] Marker sensitivities will be compared at matched-specificities; marker specificities will be compared at matched-sensitivities. The same power calculation as for Specific Aim 3 applies.

- Objective 4

Multivariable logistic regression will be used to ascertain whether 3-month finasteride PSA velocity, PCA3 and TMPRSS2:ERG add independent diagnostic information for predicting cancer outcome on biopsy relative to the PCPT risk factors in this cohort. A new biomarker will be declared to add independent diagnostic information if it retains statistical significance at the .05 level when included in the multivariable logistic regression along with all other risk factors. This analysis may have limited power since the cohort is relatively small and several risk factors will be estimated.

In addition, the approach of Ankerst et al. (2008)[24] will be used to combine the predictive information of the new biomarkers. In Specific Aim 4, we plan to upgrade the PCPT risk calculator by including the 3-month finasteride PSA velocity. In Specific Aim 5, four types of updates of the PCPT risk calculator will be examined: 1) adding a single marker (PCA3, TMPRSS2:ERG, , or PSA velocity); 2) adding two markers at a time (6 possibilities); 3) adding three markers at a time (4 possibilities); and 4) adding all four biomarkers. In each case, likelihood ratios for the biomarkers will be modeled using normal distribution (for Type 1 update) or multi-normal distribution (for Type 2-4 updates) for inclusion of new biomarkers with means conditional on PCPT risk factors. The likelihood ratios will be multiplied by the prior odds of prostate cancer of the PCPT risk calculator to form the posterior risks of prostate cancer. Risk curves and surfaces will be examined to assess the potential impact of new biomarkers as additional risk factors to the PCPT risk factors for Type 1 update and Type 2-4 updates, respectively.

*Potential pitfalls and alternative strategies for Specific Aim 5*

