As it is the primary focus, this study is mainly designed to have adequate power for Specific Aim 2 and 3, and the first three objectives of Specific Aim 5. The standard deviations in the likelihood ratios may be high resulting in updated PCPT risks with large confidence bands (high uncertainty). In this case, the observed data will assist us in planning a larger study in the future to further evaluate the independent predictive value of additional prostate cancer biomarkers and to improve the confidence interval estimations of the posterior risks of prostate cancer. A major advantage of this study design is that urine and serum samples will be reserved in the UTHSCSA biorepository. As biomarkers are discovered, it will be possible to retrospectively query study samples to address the same questions as are prospectively planned in this study for these new markers.

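### The 80% McNemar power in Section 6.3.1 does not hold for velocity against initial PSA: the protocol's own correlation gives about 63–68% at specificities of 80–90%

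*Protocol*

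**What the plan says.** Section 6.3.1 compares 3-month finasteride PSA velocity with four markers measured on the same men: initial PSA, 3-month PSA, initial DRE and 3-month DRE. One set of figures serves all four. For specificity, "with 216 controls, the study will obtain 80% power to detect increases of 8.6, 7.4, 6.1 and 4.3 percentage points in specificity" of velocity over the other markers, "when the specificities equal 80%, 85%, 90% and 95%, respectively". For sensitivity, "with 144 cancer cases, the study will have 80 percent power to detect an increase of 13.5, 15.8 and 17.8 percentage points in sensitivity", from starting values of 20%, 30% and 40%. The method is a "two-sided McNemar’s test with significance level of 0.05 using the midpoint method" from a cited paper on McNemar sample size.

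Section 6.2.1, which supports the case-control t-test, takes the SD of log PSA as 0.89 and continues: "Assuming a correlation of .5 between two PSA measures from the same patient (before and after finasteride) implies the same standard deviation" for the change. Section 6.2.2 defines velocity as the least-squares slope of log PSA on months 0, 1, 2 and 3, with higher values pointing to cancer.

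Section 6.5.4 reuses the calculation for the urine markers ("The same power calculation as for Specific Aim 3 applies"). Its pitfalls paragraph says that "this study is mainly designed to have adequate power for Specific Aim 2 and 3", together with the first three objectives of Aim 5.

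**The concern.** The power of McNemar's test depends on how often two markers disagree within a man, as well as on the difference between them. The midpoint is a default for when that rate is unknown. For velocity against initial PSA it is not free: velocity is computed from PSA values that include the initial one, and Section 6.2.1 already assumes how those values correlate. Under those assumptions, men who start high tend to fall more. Initial PSA and velocity then flag different men, discordance is close to its maximum, and power is lower than stated.

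Initial PSA is the marker that the challenge is meant to improve on. A true specificity gain of the stated size would be missed in about 32–37% of trials at specificities of 80–90%, not 20%, and a null result against initial PSA would be read as better powered than it was.

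**Working it through.** **Inputs.** Section 6.3.1: n = 216 controls and 144 cases, two-sided alpha 0.05, midpoint discordance, and the stated gains d. Section 6.2.1: correlation 0.5 and equal SDs of log PSA before and after drug. Section 6.2.2: the slope over four monthly values. Assumptions added here: bivariate normality within controls and within cases, fixed cutoffs, and equal correlation (0.5) among all four PSA values for the slope.

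**Formula.** Power = Φ[(d√n − 1.96√ψ) / √(ψ − d²)], where ψ is the discordant proportion.

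**Step 1: reproduce the stated figures.** For specificities p1 and p2 = p1 + d, the minimum ψ is d and the maximum is (1 − p1) + (1 − p2). The midpoint is therefore 1 − p1: 0.200, 0.150, 0.100 and 0.050. At 80% specificity, d√n = 0.086 × 14.70 = 1.264 and 1.96√0.200 = 0.877. The numerator is 0.387, the denominator 0.439, and power 0.811. The four specificity rows give 0.811, 0.806, 0.814 and 0.811. The three sensitivity rows (midpoint ψ = 0.335, 0.458, 0.578) give 0.806, 0.807 and 0.809. All seven agree with 80%, so the method is identified.

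**Step 2: what the midpoint implies.** Solving for the latent correlation that yields the midpoint ψ gives +0.50, +0.55, +0.59 and +0.59 for specificity, and +0.31, +0.09 and −0.20 for sensitivity.

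**Step 3: what Section 6.2.1 implies.** With change D = Y3 − Y0, Var(D) = 2σ²(1 − 0.5) = σ² and Cov(D, Y0) = 0.5σ² − σ² = −0.5σ², so corr(D, Y0) = −0.50. The slope has weights −0.3, −0.1, 0.1 and 0.3. Its covariance with Y0 is −0.3σ² + 0.5 × 0.3σ² = −0.15σ² and its SD is σ√(0.5 × 0.2) = 0.316σ, so the correlation is −0.47. By symmetry, slope against 3-month PSA is +0.47.

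**Step 4: power against initial PSA, correlation −0.47.** At 80% specificity ψ = 0.306, 1.96√ψ = 1.085, the numerator is 0.179, the denominator 0.547, and power 0.629.

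| Row | Stated gain (points) | Midpoint ψ | ψ at −0.47 | Power vs initial PSA | Power at zero correlation | Power vs 3-month PSA |
|---|---|---|---|---|---|---|
| Specificity 80% | 8.6 | 0.200 | 0.306 | 0.629 | 0.687 | 0.803 |
| Specificity 85% | 7.4 | 0.150 | 0.224 | 0.635 | 0.677 | 0.780 |
| Specificity 90% | 6.1 | 0.100 | 0.139 | 0.675 | 0.699 | 0.780 |
| Specificity 95% | 4.3 | 0.050 | 0.057 | 0.758 | 0.763 | 0.796 |
| Sensitivity 20% | 13.5 | 0.335 | 0.489 | 0.642 | 0.730 | 0.855 |
| Sensitivity 30% | 15.8 | 0.458 | 0.616 | 0.679 | 0.785 | 0.905 |
| Sensitivity 40% | 17.8 | 0.578 | 0.666 | 0.750 | 0.853 | 0.948 |

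At a correlation of −0.50 the specificity powers are 0.627, 0.634, 0.675 and 0.758, so the choice between simple change and slope does not matter.

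**Step 5: other power methods.** Simulating four correlated log PSA values per man, with fixed cutoffs, gave specificity powers of 63%, 64%, 70% and 81%. Unconditional power of the uncorrected chi-square (at −0.50) is 63%, 64%, 70% and 80%; the exact test gives 59%, 59%, 62% and 72%.

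**Step 6: gains detectable with 80% power against initial PSA.** About 10, 9, 7 and 4.5 points in specificity, and about 17, 18 and 19 points in sensitivity.

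**The case against.** Several objections are fair.

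- **The arithmetic is right.** The protocol names its convention and all seven figures follow from it. A reader might infer a calculation error; there is none. The conflict is between two planning assumptions about the same PSA values.
- **Only one comparator is affected.** A reader might infer that all of Aim 3 is underpowered. The documents do not support that. Against 3-month PSA the specificity figures hold and sensitivity power is higher than stated. For DRE no correlation is given.
- **The 0.5 was chosen for another purpose, from another population.** It serves to obtain an SD for a t-test, and 0.89 comes from the whole SABOR cohort. Entry is limited to 20–60% calculated risk, which depends partly on PSA and may narrow the initial values. As an illustration (assumed), halving the baseline SD while keeping the regression slope at 0.5 moves the correlation to about −0.28. Sensitivity power then recovers to 67%, 72% and 79%, but specificity power is still only 65–68% at 80–90%. This weakens the exact figures for sensitivity, not the conclusion for specificity.
- **Initial PSA is not singled out in the analysis text.** Section 6.3.2 expresses greater interest in specificity at matched sensitivity against all the other markers. One should not read that as naming this contrast.
- **Aim 5.** It is tempting to conclude that the reuse in Section 6.5.4 overstates power too. The protocol gives no correlation between the urine markers and velocity or the risk calculator. A zero correlation would be the reader's own assumption, and it would raise power in the 40% sensitivity row (85%).
- **Secondary status.** The comparators' operating characteristics are secondary endpoints, and the detectable specificity gains move by less than 2 points.

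**Conclusion.** The point holds for velocity against initial PSA. Under the correlation and equal SDs of Section 6.2.1, with bivariate normality and fixed cutoffs, power at the stated specificity gains is about 63%, 64% and 68% at specificities of 80%, 85% and 90%. At 95% it is about 76–81%, so little is lost there. At the stated sensitivity gains it is about 64%, 68% and 75%.

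The specificity result does not need a correlation of exactly −0.5: at zero, power at 80–90% is still only 68–70%. With equal SDs, as Section 6.2.1 assumes, the correlation of change with initial log PSA is negative for any before-after correlation below 1. To make it positive, the SD on drug would have to rise enough that 0.5 times it exceeded the SD before drug, which Section 6.2.1 does not assume.

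The 80% claim, made against all the other markers without exception, is therefore unsupported for this one. It stands for specificity against 3-month PSA and cannot be checked from the documents for DRE or the urine markers. Cutoffs set from the data, as Section 6.3.2 plans, are outside this calculation.

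**What to change.** - **Section 6.3.1:** limit the 80% statement to comparators for which midpoint discordance is consistent with Section 6.2.1. State velocity against initial PSA separately, in one of two forms: about 63–68% power at the current specificity differences for specificities of 80–90%; or approximate gains detectable with 80% power of 10, 9, 7 and 4.5 points in specificity and 17, 18 and 19 points in sensitivity. Name the assumptions (correlation 0.5, equal SDs, bivariate normality, fixed cutoffs) and keep the figures rounded. For DRE, say that the midpoint is a default.
- **Section 6.5.4, pitfalls paragraph:** qualify the statement of adequate power for Aim 3 to match.
- **Section 6.5.4, objectives 1 to 3:** at most, add that midpoint discordance is an assumption for the urine markers. No replacement figures are warranted.

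The cost is protocol wording only. Sample size, procedures and analyses are unchanged; the plan admits somewhat larger detectable differences against initial PSA.

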**6.3.2. Analysis for Specific Aim 3**

Pre-finasteride PSA and DRE and 3-month finasteride PSA and DRE will be considered as four additional markers to 3-month finasteride PSA velocity measured on the same subject. Sensitivities, specificities and AUCs (excluding the dichotomous test DRE for which the AUC cannot be computed) of these markers will be determined and compared against each other and 3-month finasteride PSA velocity. Tests of differences in the AUC between all pairs of markers (excluding DRE) will be performed using the U-statistic approach of DeLong et al., which controls for the dependencies among individuals.[67] Marker sensitivities and specificities will be compared using McNemar’s test. Comparisons will be made in 2 fashions. First, the marker sensitivities will be compared at matched-specificities, e.g., cut-offs for each marker will be found which obtain 80% specificity and then sensitivities at these cutoffs will be compared. Second, and of more interest in the application, marker specificities will be compared at matched-sensitivities. We hypothesize that 3-month finasteride PSA velocity will have increased specificity (smaller false positive rate) for a given sensitivity than the other markers.

*Potential pitfalls and alternative strategies for Specific Aim 3*

The 3-month PSA and DRE endpoint will not be available from individuals who dropped out resulting in inability to make comparisons to the primary endpoint of PSA velocity and a reduction of sample size. In anticipation of incompleters, our targeted sample size of 360 subjects is inflated by 10%, for a total of 400 enrollees.

**6.4. Specific Aim 4**: To assess the independent diagnostic value of 3-month finasteride serum PSA velocity to the Prostate Cancer Prevention Trial (PCPT) prostate cancer risk calculator.

*Rationale: Extending the rationale of Specific Aim 2, we have observed that new biomarkers may not add independent prognostic value to established risk factors including family history of disease or age, in addition to standard biomarkers. Hence the ultimate goal of this study is to establish the usefulness of 3-month finasteride PSA as an independent marker to all established biomarkers and risk factors for prostate cancer.*

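### McNemar's test at matched sensitivities or specificities ignores the sampling error of cutoffs estimated from the study cohort, so a nominal 5% test rejects in about 10–24% of null trials over the protocol's own operating range

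*Protocol*

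**What the plan says.** Section 6.3.2 fixes the test: "Marker sensitivities and specificities will be compared using McNemar’s test". It then gives two ways of matching. In the first, "cut-offs for each marker will be found which obtain 80% specificity and then sensitivities at these cutoffs will be compared". The other is the one the protocol cares about more: "Second, and of more interest in the application, marker specificities will be compared at matched-sensitivities". The Aim 3 hypothesis, that velocity has the higher specificity at a given sensitivity, is attached to that second comparison.

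No external or preset cutoffs are named for the matched comparisons. The Aim 3 rationale in 6.3 adds that "we further emphasize that the comparison be made on the same cohort".

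Precision and power are set out as follows:
- Section 6.2.1 uses the binomial formula, giving a standard error within 4.1% for sensitivity with 144 cases. For specificity, "Similarly, with 216 controls, the standard error for specificities can be controlled within 2.7" per cent.
- Section 6.3.1 repeats both standard errors and bases power on a "two-sided McNemar’s test with significance level of 0.05 using the midpoint method".
- For sensitivity, 6.3.1 says that "with 144 cancer cases, the study will have 80 percent power to detect an increase of 13.5, 15.8 and 17.8 percentage points in sensitivity" over 20%, 30% and 40%. For specificity, with 216 controls, the detectable gains are 8.6, 7.4, 6.1 and 4.3 points over 80%, 85%, 90% and 95%.
- Section 6.5.4 carries the idea into Aim 5: "Marker sensitivities will be compared at matched-specificities; marker specificities will be compared at matched-sensitivities". It reuses the Aim 3 power calculation.

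**The concern.** McNemar's test compares two binary classifications whose rules were fixed before the data were seen. Here each marker's rule is estimated. For matched specificity the cutoff is a quantile of the 216 controls, and the sensitivities are then compared in the 144 cases. For matched sensitivity it is the reverse. Each cutoff has its own sampling error, which moves the rate being compared. Unless the two markers are almost perfectly correlated, the two errors do not cancel. McNemar's variance contains no term for this, and neither do the binomial standard errors or the power figures when they are applied at matched points.

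The comparison supports the trial's practical claim of fewer unnecessary biopsies at a given sensitivity. With an anticonservative test, equally good markers would be declared different too often, and the study would look better powered for this question than it is.

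**Working it through.** **Inputs.** 144 cases, 216 controls, two-sided alpha 0.05, sensitivity 20–40% and specificity 80–95% (6.2.1, 6.3.1). Assumptions not in the protocol: equal-variance binormal markers of equal accuracy, correlation 0 to 0.9.

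**Step 1: reproduce the stated standard errors (cutoff known).** SE = √[p(1−p)/n].
- Sensitivity: √(0.40×0.60/144) = 4.08% (stated 4.1%).
- Specificity: √(0.80×0.20/216) = 2.72% (stated 2.7%).

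**Step 2: reproduce the stated power (cutoff known).** Power = Φ{[d√n − 1.96√ψ]/√(ψ − d²)}, where ψ is the midpoint between its minimum d and its maximum min(p₁+p₂, 2−p₁−p₂). For 80% versus 88.6% specificity, ψ = (0.086 + 0.314)/2 = 0.200. Power = Φ[(0.086×√216 − 1.96×√0.200)/√(0.200 − 0.0074)] = 0.81. All seven stated differences give 0.806–0.814. So 6.3.1 is arithmetically correct for known cutoffs.

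**Step 3: standard error when the cutoff is estimated.** The variance gains a second term: the squared ROC slope times the variance of the matched rate. At sensitivity 40% and specificity 80%, the slope is φ(0.253)/φ(0.842) = 1.38.
- Sensitivity at matched specificity 80%: √(0.24/144 + 1.38²×0.16/216) = 5.5% (simulation 5.6%; stated 4.1%).
- Specificity at matched sensitivity 40%: √(0.16/216 + 0.24/(144×1.38²)) = 4.0% (simulation 4.0%; stated 2.7%).

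**Step 4: type I error of McNemar's test at nominal 5%** (4,000 simulated trials per setting, empirical cutoffs):

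| Matched on | Rejection rate, equal markers |
|---|---|
| Specificity 80% | 15–16% |
| Specificity 85% | 16–18% |
| Specificity 90% | 18–20% |
| Specificity 95% | 21–24% |
| Sensitivity 40% (specificity 80%) | 16–18% |
| Sensitivity 30% (specificity 90%) | 13–15% |
| Sensitivity 20% (specificity 95%) | 10–13% |
| Sensitivity 80% (not stated in the protocol) | 25–26% |
| Sensitivity 90% (not stated) | 29–32% |
| Sensitivity 95% (not stated) | 30–34% |

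With the true cutoffs, the same test rejects in 4–6% of trials, so the excess comes from estimating them. At specificity 80% and correlation 0.5, the sensitivity difference has an actual SD of 6.5 points, against a mean McNemar standard error of 4.7. Continuity-corrected and exact versions are also inflated in nearly all settings.

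**Step 5: a valid test.** A stratified bootstrap that re-estimates both cutoffs in every resample (1,000 trials, 300 resamples, correlation 0.5) rejects in about 4–6% of null trials, and in 2.3% at sensitivity 20%/specificity 95%. Its power at the stated differences, against the planned 80%:
- 40% versus 57.8% sensitivity at specificity 80%: about 75%.
- 20% versus 33.5% sensitivity at specificity 95%: about 39%.
- 80% versus 88.6% specificity at sensitivity 40%: about 50%.

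**The case against.** Several points on the other side stand, and they limit the finding.

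- **The primary analysis survives.** The primary endpoint concerns velocity's own operating characteristics. Section 6.2.2 tests AUC = 0.5 with the Wilcoxon/U-statistic, and 6.3.2 compares AUCs by DeLong's method. Neither uses a matched cutoff. A reader might infer that the trial's main inference fails; the protocol does not support that.
- **An error rate near 30% is not the headline.** It needs matched sensitivities of 80–95%. Such values would suit a test meant to spare biopsies, but the protocol names none and works at 20–40%.
- **The stated standard errors are not miscalculated.** They reproduce, and they suit the fixed range of velocity cutoffs in 6.2.2. They fall short only at matched points.
- **The matched-sensitivity comparison is not the worst affected in the stated range.** One might expect it to be, because its cutoff comes from the smaller group. The rates are 10–18% there and 15–24% at matched specificity.
- **The men are not used twice in the obvious sense.** Cutoffs come from one disease group and the test is run in the other. The fault is omitted cutoff variance.
- **Aim 5 is partly inference.** Section 6.5.4 names no test for its matched comparisons; it only carries over the Aim 3 power calculation.
- **Some stated power is conservative.** For 40% versus 57.8% sensitivity the midpoint ψ is 0.578, above the 0.40×0.422 + 0.578×0.60 = 0.516 implied by independent errors. This helps explain why power there falls only to about 75%.

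None of this rescues the test itself. The AUC analyses do not address the hypothesis of higher specificity at a given sensitivity. Section 6.2.1 itself justifies the sample size by interest in specificity at a fixed sensitivity, which is the matched setting.

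**Conclusion.** The concern holds for the matched-point comparisons. As written, McNemar's test with cohort-derived cutoffs has a type I error of about two to nearly five times nominal over the protocol's own range (10–24%), rising to 25–34% only at high matched sensitivities that the protocol does not state. Matched-point standard errors at 40%/80% are about 5.6% and 4.0%, which is 1.4 to 1.5 times the stated 4.1% and 2.7%. The 80% power in 6.3.1 holds only for known cutoffs.

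The exact sizes rest on equal-variance binormal markers, and the power figures on correlation 0.5. The direction does not depend on these choices: every setting examined was inflated with estimated cutoffs and near 5% with true ones. The conclusion also assumes that the cutoffs are found in the study data, which is the natural reading of 6.3.2.

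**What to change.** 1. In 6.3.2, replace McNemar's test for every matched-point comparison with a stratified bootstrap. Resample cases and controls separately, re-derive the matched target and each marker's cutoff in every resample, and take the standard error, confidence interval and test of the difference from it.
2. Include velocity against DRE when velocity is matched to DRE's observed sensitivity or specificity. DRE has no adjustable cutoff, but the target it supplies is itself estimated and must be re-derived in each resample.
3. Keep McNemar's test only where both classifications use cutoffs fixed before the data.
4. In 6.2.1 and 6.3.1, say that 4.1% and 2.7% apply to preset cutoffs. Restate matched-point precision and the detectable differences in 6.3.1 with cutoff error included.
5. In 6.5.4, name the same method for the matched comparisons and refer to the restated power.

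The cost is revised wording, a little more programming, and less favourable stated precision and detectable differences. No additional patients or procedures are needed, and the AUC analyses stay as they are.
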